## Abstract

**Background:**

Cerebral palsy (CP) is a group of permanent but nonprogressive disorders that affect movement and posture, often accompanied by upper extremity impairments such as abnormal muscle tone, spasticity, weakness, and impaired motor control. Neuromuscular electrical stimulation (NMES) and Leap Motion–based interventions that promote neuroplasticity through different mechanisms. However, studies directly comparing these 2 approaches in children with spastic CP are limited.

**Objective:**

This study primarily aims to investigate the effects of NMES and Leap Motion–based exercise interventions on hand function in children with spastic CP and to compare the effectiveness of these 2 modalities. The secondary objective is to evaluate and compare the effects of these interventions on wrist extensor muscle activation, wrist joint range of motion, selective motor control, and hand use in daily activities.

**Methods:**

This study is a 2-arm, parallel-group randomized controlled trial with a 1:1 allocation ratio and will include 30 children aged 6‐15 years with spastic CP and distal upper extremity involvement. All participants meeting the inclusion criteria will undergo baseline assessments at T0, where wrist range of motion will be measured using an electronic goniometer; selective motor control will be evaluated using the Selective Control of the Upper Extremity Scale (SCUES); hand function will be assessed using the Jebsen-Taylor Hand Function Test; daily hand use will be evaluated using the ABILHAND-Kids questionnaire; and wrist extensor and flexor muscle activation will be assessed using surface electromyography (sEMG). All participants will then undergo a 4-week conventional exercise program (3 sessions per week, 40 minutes per session). At the end of the 4 weeks, all baseline measurements will be repeated (T1). Subsequently, participants will be randomly assigned into 2 groups: the Leap Motion group (n=15) and the NMES group (n=15). Both groups will participate in an 8-week exercise program consisting of 3 sessions per week, 60 minutes per session (including 20 minutes of either Leap Motion–based exercise or NMES application, followed by 40 minutes of conventional exercise). At the end of this 8-week program, all assessments will be repeated (T2).

**Results:**

Data collection started in January 2026. The study is expected to be completed by September 2026.

**Conclusions:**

To our knowledge, the study will be the first randomized controlled study to evaluate and compare the effects of NMES and Leap Motion–based training on hand functions in children with spastic CP. The findings are expected to contribute to evidence-based clinical practice by guiding the selection of effective upper extremity rehabilitation strategies for pediatric populations. Findings may inform future rehabilitation protocols by highlighting the benefits of integrating advanced technology-based interventions alongside conventional therapy approaches.

## Introduction

Cerebral palsy (CP) is a group of disorders arising from permanent, nonprogressive damage to the developing brain, which affects movement and postural development, leading to activity limitations. While the primary issue in CP is motor dysfunction, sensory, perceptual, cognitive, and communicative impairments may also be observed [1]. In 2000, the European Cerebral Palsy Surveillance Group conducted an epidemiological study across 16 countries to develop a more advanced classification system, classifying CP based on the distribution of motor impairment as unilateral or bilateral and according to motor type as spastic, dyskinetic, ataxic, or mixed [2]. Spastic CP results from involvement of the motor cortex and the white matter projections entering and exiting the sensorimotor area. Spastic CP is the most common motor type of CP, with a prevalence of 85%‐90%, of which one-third are unilateral and two-thirds are bilateral [3].

In children with spastic CP, upper extremity involvement is observed in approximately 50%‐70% of cases [4]. Upper extremity functionality is crucial for children’s participation in daily life and overall quality of life. While these functions play an important role in performing independence-requiring activities such as reaching, grasping, releasing, and self-care, as well as supporting the individual’s activity participation, impaired hand function negatively affects activity performance and participation skills [5]. Upper extremity disorders in CP may include abnormal muscle tone, imbalance between agonist and antagonist muscles, spasticity, alignment problems, reduced muscle strength, and impaired motor control. Consequently, hand use is typically affected, hindering the performance of daily living activities. Stereotypical postures such as wrist flexion with ulnar deviation and flexion of the fingers and thumb toward the palm make grasping and releasing skills difficult [3,6].

Conventional management of the upper extremity in children with CP typically involves physiotherapy-based interventions, including stretching, strengthening exercises, positioning strategies, splinting, casting, and movement facilitation [7]. With technological advancements in rehabilitation, evidence-based upper extremity interventions have expanded to include action observation therapy, constraint-induced movement therapy, hand-arm bimanual intensive training, repetitive transcranial magnetic stimulation, neuromuscular electrical stimulation (NMES), virtual reality (VR)–based games, and goal-directed and task-oriented training [8].

NMES has been used for various purposes, including spasticity inhibition, prevention of muscle atrophy, enhancement of muscle metabolism and enzyme activity, facilitation of isolated muscle contraction, neuromuscular facilitation of voluntary isolated muscle contraction, promotion of nerve regeneration, maintenance or improvement of normal joint movements, and modification of muscle contractile properties [9,10]. Electrical stimulation can evoke impulses that travel orthodromically through motor axons toward the target muscle, leading to muscle contraction. These impulses may also travel antidromically toward the central nervous system, potentially inducing short- and long-term neurophysiological changes in spinal reflex circuits, corticospinal pathways, and cortical networks, thereby contributing to neuroplastic modulation [11]. This study reports that NMES application to the upper extremities in children with CP is less common than its use in the lower extremity and is generally combined with orthoses or applied following botulinum toxin type A injections [10]. A systematic review reported positive effects of NMES on increasing muscle strength, reducing spasticity, improving range of motion (ROM), and enhancing hand function in children with CP [12]. However, Faccioli et al [8] indicated that there is inconclusive evidence regarding the effectiveness of NMES in improving upper extremity function in CP.

VR-based rehabilitation may support functional recovery in children with CP by promoting neuroplastic mechanisms. Repetitive, intensive, and multisensory practice can facilitate activity-dependent neural adaptation by strengthening existing neural connections and supporting the use of alternative neural pathways [13]. Through visual, auditory, and proprioceptive feedback, VR environments may engage several brain regions involved in motor planning, sensorimotor integration, attention, and movement control, thereby contributing to upper extremity motor learning [14]. The therapeutic models for upper extremity rehabilitation focus on high-intensity, repetitive, and task-specific exercises. However, combining technology and visually interactive systems with physiotherapy devices has become increasingly common, which can enhance children’s motivation and adherence to therapy [15,16]. VR interventions provide a unique, immersive environment in which patients can engage in interactive and stimulating activities tailored to their individual needs and abilities [17]. Studies in the literature that have applied VR in upper extremity rehabilitation for CP have generally focused on upper extremity dysfunction, spasticity, and muscle weakness [18,19].

Video-based game therapy models do not detect the hand and finger movements necessary for training fine motor skills. This limitation can be overcome using the Leap Motion Controller (LMC; Leap Motion, Inc), a VR method. The LMC is designed to detect, recognize, and capture hand movements and finger positions in interactive software applications. Additionally, it allows tracking of arm, wrist, and hand positions for up to 4 participants simultaneously [20]. The LMC has been reported to be highly accurate in detecting wrist flexion/extension and radial/ulnar deviation movements, but less accurate for forearm supination and pronation [21]. This study includes several studies investigating the contribution of LMC to hand function in patients with CP, stroke, spinal cord injury, and multiple sclerosis [22-25]. However, studies examining the use of the LMC in upper extremity rehabilitation for CP are quite limited.

In the literature on upper extremity interventions in CP, no study has compared LMC-based intervention with an alternative therapeutic modality. In contrast to existing studies, the present study will compare the effects of an LMC-based intervention on hand function parameters with those of NMES in children with CP, thereby evaluating the impact of 2 different interventions on hand function. This approach will enable a comparison between a traditional modality currently used in the treatment of hand function in children with CP and a recently introduced, technology-based, game-oriented therapy method. This direct comparison was considered necessary to provide clinically relevant information on which approach may be more effective for improving hand function outcomes in children with spastic CP. Furthermore, by incorporating surface electromyography (sEMG), this study aims to objectively assess changes in wrist extensor and flexor muscle activation and to explore the neuromuscular mechanisms underlying functional improvements beyond clinical outcome measures. We hypothesize that Leap Motion–based intervention will provide greater improvements in hand function parameters than NMES in children with CP.

## Methods

### Participants

The sample size was calculated using the G*Power (version 3.1.9.7; Heinrich Heine University Düsseldorf, Düsseldorf) program, with the Jebsen-Taylor Hand Function Test (JTHFT) selected as the primary outcome measure and an assumed effect size of *f*=0.5 selected with reference to a previous study [26]. The calculation was performed with a statistical power of 95% and α=.05, in line with previous research using technology-assisted intervention in CP [27], yielding a minimum required sample size of 24 participants. Considering a 20% attrition rate, a total of 30 participants, with 15 participants in each group, was considered appropriate. The sample size calculation was based only on the primary outcome measure; secondary outcomes were considered exploratory and were not independently used for power estimation.

### Inclusion Criteria for the Study Are as Follows

Diagnosis of spastic unilateral or bilateral CP confirmed by clinical and magnetic resonance imaging findings, involvement of the distal upper extremity (wrist and/or fingers), being between 6 and 15 years of age, no botulinum toxin injections or surgical interventions applied to the upper extremity within the past 6 months, Gross Motor Function Classification System (GMFCS) levels 1-3, Manual Ability Classification System (MACS) levels 1-3, upper extremity spasticity graded as 0, 1, or 1+ according to the Modified Ashworth Scale (MAS), passive wrist extension angle limitation not exceeding 10 degrees, and ability to follow instructions (mental level documented as “normal” or “mild intellectual disability” in the medical report.

Exclusion criteria were defined as follows: enrollment in a specific hand rehabilitation program at the time of this writing, presence of visual or hearing impairments, history of epilepsy, and presence of chronic, orthopedic, or other systemic conditions that may interfere with participation in the study.

### Patient Withdrawal Criteria

Participants who fail to attend 6 consecutive sessions (2 weeks), attend less than 80% of the total sessions, or develop an unexpected neurological condition (eg, epilepsy) during the study will be excluded from the analysis.

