### Outcome Measures

The primary outcome of this study is hand function, and the secondary outcomes are wrist extensor and flexor muscle activation, wrist ROM, wrist selective motor control, and hand use in daily activities. The baseline assessments (T0) will be done after enrollment. Before randomization, all participants will complete a 4-week standardized upper extremity–focused conventional therapy program, which will be conducted as a baseline standardization period to reduce the potential influence of previous routine rehabilitation programs. This phase will not be considered part of the randomized intervention comparison. Postconventional exercise assessments (T1) will be conducted after a 4-week conventional therapy program. Randomization will be performed after the T1 assessment to allow comparison of the additional effects of NMES and Leap Motion–based training when added to the standardized conventional exercise program. The final assessments (T2) will be performed after 8-week NMES and Leap Motion–based interventions. The main comparison will be based on the change from T1 to T2 between the intervention groups. A randomized controlled design was selected to minimize selection bias and to ensure balanced baseline characteristics between the intervention groups. The inclusion of 3 assessment time points (T0, T1, and T2) allows differentiation between the effects of conventional therapy and intervention-specific effects.

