### Statistics

Statistical analyses will be performed using SPSS for Windows (version 25.0; IBM Corp). Descriptive statistics will be calculated for all variables. Continuous variables with normal distribution will be presented as mean (SD), continuous variables without normal distribution as median (minimum-maximum), and categorical variables as frequency and percentage. The normality of continuous variables will be assessed using the Shapiro-Wilk test. The primary intervention effects will be analyzed using a 2-way repeated measures ANOVA to evaluate the main effects of group and time, as well as the group×time interaction. When significant main or interaction effects are detected, post hoc pairwise comparisons will be performed with Bonferroni correction for multiple comparisons. For variables that do not meet the assumptions for parametric analysis, appropriate nonparametric alternatives will be used. Categorical variables will be analyzed using the chi-square test or Fisher exact test, depending on the expected cell counts. The primary analysis will be conducted as a complete-case analysis, including only participants who complete all assessment time points. Dropouts and missing data will be documented. Effect sizes will be reported to support the interpretation of the magnitude of intervention effects. Partial eta squared will be reported for repeated measures ANOVA results. A *P* value of <.05 will be considered statistically significant.

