Several potential limitations of this study should be acknowledged. First, the relatively small sample size should be considered when interpreting the findings. Due to the nature of the interventions, blinding of participants and therapists is not feasible, which may introduce performance bias. Because all participants will receive the same standardized conventional therapy before randomization, this phase is expected to reduce between-participant variability rather than introduce differential bias between groups. However, the possible influence of this pre-randomization phase on subsequent responses to the randomized interventions will be considered when interpreting the findings. The absence of long-term follow-up assessments restricts the ability to determine the persistence of intervention effects over time. Additionally, the game-based and interactive nature of the Leap Motion–based intervention may increase participant motivation and engagement, which may introduce potential motivational bias. Future studies with larger sample sizes, longer follow-up periods, and combined or additive intervention models may further clarify the long-term and comparative effects of these approaches.

After completion of the study, the findings will be disseminated through peer-reviewed publication and scientific meetings, with the aim of informing evidence-based upper extremity rehabilitation practices for children with CP.

In conclusion, this study is expected to contribute to the literature by providing clinically relevant evidence on the comparative effects of 2 interventions based on different neuroplasticity stimulation mechanisms in pediatric upper extremity rehabilitation. The integration of clinical outcome measures with objective sEMG assessment may offer a more comprehensive understanding of wrist muscle activation and functional changes in children with spastic CP. The findings may guide the selection of intervention methods, support evidence-based rehabilitation protocols, and contribute to the applicability of different modalities in clinical practice.

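### The primary analysis keeps only complete cases who met attendance rules and had no new neurological condition, so it omits some randomised children and may bias the T1 to T2 comparison

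*Protocol article*

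**What the plan says.** Two parts of the protocol article together define who is analysed.

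- **Patient Withdrawal Criteria.** The rule opens with long absence: "Participants who fail to attend 6 consecutive sessions (2 weeks"). It continues with those who "attend less than 80% of the total sessions, or develop an unexpected neurological condition (eg, epilepsy) during the study will be excluded" from the analysis. It concerns the analysis, not only continued treatment.
- **Statistics.** "The primary analysis will be conducted as a complete-case analysis, including only participants who complete all assessment time points". For children who fall outside this set, the section adds only: "Dropouts and missing data will be documented".

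The timing comes from Outcome Measures: "Randomization will be performed after the T1 assessment", and "The main comparison will be based on the change from T1 to T2 between the intervention groups".

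Three other places bear on whether exclusion could depend on the arm. The Introduction says that technology-based, interactive systems can improve children's motivation and adherence. The limitations paragraph of the Discussion says that the game-based format "may increase participant motivation and engagement". Randomization and Allocation states that participants and the treating physiotherapist cannot be blinded.

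**The concern.** Randomisation makes the two arms comparable as complete groups. Once children are removed for something that happens after allocation, that protection holds for the remaining children only if removal is unrelated to how they would have responded, or is related to it in the same way in both arms. Attendance over 8 weeks of unblinded treatment, in which one arm plays games and the other receives electrical stimulation, is not a safe candidate for that assumption.

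At stake is the meaning of the main result. The article sets out to say which approach improves hand function more. The stated set answers a narrower question, about children who attended well, stayed neurologically stable and completed every assessment, and the children meeting that description may differ between arms. With 15 children per arm, a few exclusions are enough to matter.

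**Working it through.** **1. The plan's own figures.** The Participants section gives a minimum of 24, 20% attrition and a total of 30. Check: 24 / (1 − 0.20) = 30, which reproduces. The minimum of 24 also reproduces for a group × time interaction with f = 0.5, α = 0.05, 2 groups, 3 time points and a correlation of 0 between time points (this correlation is an assumption; the article gives none). The noncentrality is λ = f² × N × 3 = 0.25 × 24 × 3 = 18 on 2 and 44 degrees of freedom, giving power 0.965. N = 22 gives 0.948. At N = 30, λ = 22.5 on 2 and 56 degrees of freedom and power is 0.990. On this basis the loss of 6 of 30 children costs little power. The allowance covers numbers; it says nothing about which children are lost.

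**2. What the 80% rule removes.** There are 8 × 3 = 24 sessions after randomisation and 4 × 3 = 12 before it, 36 in all.
- If the rule refers to 24: 0.80 × 24 = 19.2, so a child who misses 5 or more is removed.
- If it refers to 36: 0.80 × 36 = 28.8, so a child who misses 8 or more is removed.

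The text speaks of total sessions and does not say which is meant, so two analysts could form different sets.

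**3. Shift when exclusion rates differ.** Exclusion rates and the attendance–outcome correlation are not in the article; all are assumed. Let the lowest fraction p of one arm and q of the other be excluded on a normal attendance scale that correlates ρ with the outcome change. The shift in the between-arm difference, in SD of the change, is

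ρ × [φ(z_p)/(1 − p) − φ(z_q)/(1 − q)],

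where φ is the normal density and z the normal quantile.

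| p v q | φ(z_p)/(1 − p) | φ(z_q)/(1 − q) | Difference | ρ = 0.3 | ρ = 0.5 |
|---|---|---|---|---|---|
| 20% v 7% | 0.350 | 0.144 | 0.206 | 0.06 SD | 0.10 SD |
| 30% v 10% | 0.497 | 0.195 | 0.302 | 0.09 SD | 0.15 SD |

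For scale, the standard error of the difference with 15 per arm is √(2/15) = 0.37 SD.

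**4. Equal exclusion rates do not guarantee safety.** Suppose there is no true effect and 20% are excluded in each arm, at random in one arm and correlated ρ with outcome in the other. The formula gives ρ × 0.350. A simulation with 15 per arm and a nominal 5% test agrees:

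| ρ | Formula | Simulated bias | Type I error |
|---|---|---|---|
| 0 | 0 | about 0 | 5.0% |
| 0.3 | 0.10 SD | 0.11 SD | 5.9% |
| 0.5 | 0.17 SD | 0.18 SD | 7.1% |
| 0.7 | 0.24 SD | 0.25 SD | 9.1% |

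This is a deliberately one-sided case. It shows that similar numbers excluded per arm would not by themselves be reassuring.

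**The case against.** The strongest reply is that the harm is small and unproven. Every input to the bias calculation is assumed, and 0.06 to 0.15 SD is less than half the standard error of 0.37 SD. If the game arm attends better and attendance goes with better response, more poor responders leave the NMES arm. That flatters NMES and so works against the article's own hypothesis that Leap Motion is superior. This stands as a limit on size. The direction holds only in that scenario, however, and a bias smaller than the standard error is still one that nothing in the stated plan removes.

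A second reply is that an analysis of all randomised children may sit in an unseen analysis plan. It might, as a secondary analysis. The article nevertheless names the primary set itself, so the point concerns what is stated, not what is left out.

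Several stronger readings are tempting and are not supported:

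- **That children are not compared by randomised group.** Nobody is moved between arms. Those retained are compared as allocated; the fault is that not everyone is retained.
- **That the article expects exclusion to differ by arm.** The Introduction and Discussion say only that motivation, adherence or engagement can or may rise. Differential exclusion is a plausible inference, no more.
- **That requiring T0, or counting run-in absences, biases the comparison through allocation.** T0 and the 12 run-in sessions precede randomisation, so allocation cannot cause a missing T0 or a run-in absence. Children excluded before randomisation do not bias the comparison. What remains is the ambiguity about 24 or 36 sessions.
- **That excluding a child with new-onset epilepsy hides a safety event.** The article provides for recording adverse events in both intervention sections. What the comparison loses is that child's hand-function outcome.
- **That children with a T2 measurement are being discarded in numbers.** The article does not say whether withdrawn children are assessed at T2.
- **That the rule costs material power.** A two-sample test at 1.0 SD would fall from 75% (15 per arm) to 65% (12 per arm), but that is not the article's calculation, and the 20% allowance already plans for six losses.

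**Conclusion.** The point holds in this form: the stated primary analysis is restricted to complete cases who met attendance rules and had no new neurological condition, so it does not include all randomised children. Because exclusion during the 8-week period can depend on allocation, the T1 to T2 comparison may be biased. Bias is possible, not established. Under differential exclusion of 20% v 7% to 30% v 10% and correlations of 0.3 to 0.5 it is modest, about 0.06 to 0.15 SD, and its direction depends on how exclusion relates to response in each arm. The article gives neither the exclusion rates nor the correlations. The issue deserves correction despite the modest size, because it lies in the primary analysis set of a 30-child randomised trial and is cheap to remove. The Results section reports 11 children enrolled as of June 2026, with analysis to follow only once all have finished, so the change can still be made before any analysis.

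**What to change.** - Separate stopping the intervention from exclusion from the analysis. This changes nothing about when a child's sessions stop.
- Define the primary analysis set as all randomised children in their allocated arm, whatever their attendance or new diagnoses.
- Seek the planned T2 assessment from every child who has not withdrawn consent, whatever the attendance.
- Replace the complete-case rule with a likelihood-based mixed model, or multiple imputation, using the available T0 and T1 data for a missing T2 (or T0), and state the missing-data assumption.
- Keep the 80% attendance set as a labelled secondary (per-protocol) analysis, and state whether 80% refers to the 24 post-randomisation sessions or to all 36.
- Report exclusions from that secondary set, and any new neurological condition, by arm.

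The cost is a change of analysis wording and some effort to obtain T2 from poor attenders. The downside is a slightly diluted estimate if non-attendance is common. A T2 value that cannot be obtained is not fully recovered by modelling, so the effort spent on obtaining T2 matters more than the choice of method. The number to recruit does not change.
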